### Data collection

All study data, including research-specific instruments and clinical forms, will be stored in both physical file folders and on a password-protected personal computer under the direct responsibility of the principal investigators. To ensure confidentiality, participants will be de-identified using unique numerical codes.

At baseline, a Case Report Form (CRF) will record demographics (age, sex), oncological diagnosis, and comorbidities. During each PBMT session, participants will undergo systematic clinical evaluation. Any clinical changes, adverse reactions, or OM progression will be documented on a standardized longitudinal follow-up form to monitor the incidence and trajectory of oral lesions throughout treatment.

The primary clinical endpoint:

OM severity

Will be assessed by a trained examiner at each clinical visit. To ensure a comprehensive evaluation of both functional and clinical aspects, severity will be graded according to the established criteria of the World Health Organization (WHO) and the National Cancer Institute Common Terminology Criteria for Adverse Events (NCI-CTCAE) [31] (Table 2).

The WHO scale will be used to integrate objective clinical signs (erythema and ulceration) with the patient’s functional ability to maintain oral intake. Simultaneously, the NCI-CTCAE scale will provide a standardized grading of symptomatic and clinical toxicity. The detailed scoring criteria for both instruments are summarized in Table 2.

**Table 2 Tab2:** Classification of OM according to the WHO and NCI scales

Scales	WHO	NCI
0	Normal mucosa	Normal mucosa
1	Erythema	Erythema
2	Ulcer, normal diet	Non-contiguous ulcers up to 1.5 cm in diameter
3	Ulcer, liquid diet	Contiguous ulcers larger than 1.5 cm in diameter
4	Ulcer, unable to tolerate oral intake	Ulcers with necrosis and bleeding

2.)Topographic mapping of oral lesions

To accurately track the progression and resolution of OM, a systematic topographic mapping of the oral cavity will be performed during each clinical evaluation. The presence, extension, and anatomical location of erythema and ulcerative lesions will be documented using a standardized oral cavity map.

The assessment will encompass the following anatomical sites:

Non-keratinized mucosa: Buccal mucosa, labial mucosa, ventral/ lateral tongue, soft palate, and floor of the mouth.Keratinized mucosa: Dorsum of tongue and hard palate.

The examiner will record specific sub-sites and lesion surface area, enabling comparative analysis of TC versus IO PBMT efficacy in reaching anatomically shielded regions, such as the oropharynx and tongue base. The ulcerated area will be quantified through topographic mapping, estimation of the lesion’s extent in cm² using a clinical ruler, and standardized digital intraoral photography.

3.) Pain

The Numerical Rating Scale (NRS) for pain consists of an 11-point scale ranging from 0 to 10, where 0 represents “no pain/difficulty” and 10 indicates the “worst pain/difficulty imaginable.” Patients are asked to choose a whole number that best describes the intensity of the pain or difficulty they are experiencing, facilitating a quick and objective quantification of the painful experience [32].

Assessments will be conducted at baseline, immediately following each PBMT session, and during all subsequent follow-up visits. This longitudinal monitoring aims to evaluate the patient’s symptomatic response to the intervention over time. Participants will be instructed to mark the point on the scale that most accurately represents their current status for each evaluated parameter, providing a quantitative measure of subjective treatment impact.

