## Abstract

This study aims to compare the clinical efficacy of transcutaneous photobiomodulation (PBMT) with an 808 nm infrared laser versus intraoral PBMT with a 660 nm red laser in the prevention of oral mucositis (OM). The study is designed to assess whether the transcutaneous approach is non-inferior to the intraoral standard, thereby contributing to the optimization and standardization of PBMT protocols in head and neck cancer (HNC) supportive care. Methods: A randomized pilot study is being conducted with 54 patients (*n* = 27 per group) undergoing radiotherapy (60–70 Gy) for HNC. Participants will be randomly assigned to receive either intraoral PBMT (660 nm, 100 mW, 1 J/point, fluence = 10.20 J/ cm², 10 s, 44 points) or transcutaneous PBMT (808 nm, 100 mW, 1 J/point, fluence = 34.5 J/ cm² (central) and 4.3 J/ cm² (lateral), 10 s, 32 points). Interventions occur three times weekly throughout treatment. The primary outcome is OM severity, graded by WHO scale. Secondary outcomes include OM severity (NCI-CTCAE), pain intensity (Numeric Rating Scale, NRS), ulcerated area extension, registered through digital images, treatment interruptions and unscheduled healthcare utilization. Expected outcomes: the primary hypothesis posits that transcutaneous infrared PBMT is as effective as intraoral red PBMT in mitigating OM severity. Additionally, the transcutaneous approach is expected to offer logistical advantages, including a reduction in application time (80 s vs. 440 s) and improved tolerability in patients with radiation-induced trismus or severe oral pain. Conclusion: This protocol is expected to provide robust evidence to support the most feasible and effective PBMT modality for OM prevention. By optimizing treatment delivery, the study may enhance adherence, preserve nutritional status, and improve the quality of life for patients undergoing oncological therapy.

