### Secondary outcomes

Compare IO and TC PBMT regarding:

OM severity (NCI-CTCAE);Pain intensity (NRS);Ulcerated area extension (grades 2–4) will be registered with digital images;Treatment interruptions (unplanned RT/CRT modifications);Unscheduled healthcare utilization (emergency visits or hospitalizations due to OM complications).

This study explores PBMT delivery routes to standardize application parameters and optimize supportive care for patients with head and neck malignancies.

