### Expected results

This study generates comparative data on TC (infrared) versus IO (red) PBMT efficacy for OM prevention during head and neck radiotherapy.

The primary hypothesis is that TC PBMT is non-inferior or superior to IO PBMT in preventing OM. Furthermore, TC PBMT improves compliance in patients with trismus or limited mouth opening, as it obviates the need for prolonged intraoral access during treatment.

Regarding the outcomes of pain and ulcerated area extent, transcutaneous PBMT is expected to demonstrate efficacy equivalent to or superior to that of intraoral PBMT, providing significant relief of pain symptoms through its greater tissue penetration depth and modulation of inflammation.

Furthermore, the results support the development of standardized, evidence-based protocols for the implementation of PBMT in clinical settings, ensuring the consistent and reliable application of this therapy across various patient subgroups. Consequently, this research will provide baseline data for future proposals, serving as a foundation for larger-scale multicenter trials and longitudinal evaluations of the efficacy and safety of photobiomodulation.

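### The pain outcome is named as pain intensity, but its 0–10 scale is worded for pain or an undefined difficulty, so the score may mix the two

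*Protocol article*

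**What the plan says.** The outcome is named the same way throughout. The Abstract lists pain intensity on the NRS among the secondary outcomes, the Secondary outcomes section lists "Pain intensity (NRS"), and the Statistical analysis section assigns pain intensity to a longitudinal mixed-effects model.

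The instrument is described in Data collection, item 3 (Pain). It opens with pain alone: "The Numerical Rating Scale (NRS) for pain consists of an 11-point scale ranging from 0 to 10". The anchors then widen: "where 0 represents “no pain/difficulty" at the lower end and "10 indicates the “worst pain/difficulty imaginable" at the upper end. The patient is to "choose a whole number that best describes the intensity of the pain or difficulty they are experiencing", and the sentence ends by saying that this number quantifies how painful the experience is.

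The item closes with: "Participants will be instructed to mark the point on the scale that most accurately represents their current status for each evaluated parameter". No parameter other than pain is named there.

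**The concern.** An outcome called pain intensity should be measured by a question about pain. Here the name and the stated purpose say pain, while both anchors and the instruction say pain or difficulty. A patient with little pain but marked difficulty swallowing could give a low or a high number, and both would follow the instruction.

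The interpretation of one secondary outcome is at stake. Expected results anticipates that transcutaneous PBMT will match or exceed intraoral PBMT on pain, so the NRS comparison will be read as evidence about pain relief. If some answers reflect difficulty, neither a difference nor the lack of one can be clearly assigned to pain. Once a single number has been recorded, no model can divide it.

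**Working it through.** The article gives no figure for pain: no expected difference, standard deviation, margin or power. There is nothing to reproduce. The margin of 0.5, one-sided α of 0.025, 80% power and 54 participants in Sample size all belong to the WHO scale. The check is therefore a comparison of the texts, followed by a short argument about direction.

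**Step 1. Name against instrument.**

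| Place | Construct |
|---|---|
| Abstract; Secondary outcomes; Statistical analysis | pain intensity |
| Data collection, Pain: name of scale and stated purpose | pain |
| Data collection, Pain: lower anchor, upper anchor, patient instruction | pain or difficulty |
| Data collection, Pain: closing sentence | several parameters, not named |

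Difficulty is not defined, and it appears in neither the outcome list nor the analysis.

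**Step 2. The two possible readings.**

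- *One item.* The single number covers pain or difficulty, and the score is a mixture.
- *Several items with shared generic anchors.* Pain is rated alone and difficulty is rated separately. There is then no mixing, but at least one difficulty item is collected that is not identified, listed or analysed.

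The text does not decide between them. Both need a correction.

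**Step 3. Could difficulty behave differently from pain across the arms?** The article gives grounds to think it could, without any figure:

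- The Introduction treats trouble eating or swallowing as characteristic of oral mucositis, so difficulty may track the disease.
- The Discussion cites a randomised trial in which the two routes were equivalent across mucositis grades, yet swallowing difficulty was lower with the transcutaneous route.
- The Discussion also says the intraoral route is more affected by trismus and may be uncomfortable for patients in severe pain.
- The NRS is taken straight after every PBMT session, in an open-label trial.

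**Step 4. Direction.** Let the recorded score be S = (1 − w)P + wD, with P pain, D difficulty and w the weight on difficulty. The arm difference is

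δ_S = (1 − w)δ_P + wδ_D.

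For a positive δ_P, it is smaller than δ_P if δ_D < δ_P, equal if δ_D = δ_P, and larger if δ_D > δ_P. On the standardised scale, with equal standard deviations and correlation r,

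d_S = [(1 − w)d_P + w·d_D] / √[(1 − w)² + w² + 2rw(1 − w)].

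The following inputs are all assumed and serve only to show that the direction is open. With d_P = 0.80:

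- w = 0.5, r = 0.9, d_D = 0: 0.40 / √0.95 = 0.41 (smaller).
- w = 0.25, r = 0.9, d_D = 0.8: 0.80 / √0.9625 = 0.82 (almost unchanged).
- w = 0.5, r = 0.3, d_D = 1.2: 1.00 / √0.65 = 1.24 (larger).

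The article supplies none of w, r, d_P or d_D. These values are not estimates for this trial.

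**The case against.** The strongest reply is that mixing is only one reading. The item is headed Pain, calls the tool an NRS for pain and says it measures the painful experience. The closing reference to evaluated parameters fits a generic 0–10 format applied to separate questions. The article condenses a fuller protocol, and Data collection mentions research-specific instruments and forms that are not shown, so the form may ask about pain alone. The wording is also the same in both arms, and pain is one of five secondary outcomes in a self-described pilot.

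Most of this stands, and it limits the point to what the score *may* do. It does not remove the point. The anchors and the instruction are stated explicitly, so this is not a detail left to another document. The benign reading still leaves an unidentified item. Identical wording does not guarantee a harmless comparison if difficulty differs by route.

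A reader might also infer three things that the document does not support:

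- *That the two response instructions conflict.* On an 11-point whole-number scale, marking a point is choosing a number.
- *That the trismus statement shows how patients will answer.* Expected results says "TC PBMT improves compliance in patients with trismus or limited mouth opening", which concerns compliance and says nothing about the NRS.
- *That difficulty is unrelated to route, so a pain difference must be diluted.* The Introduction and the cited trial in the Discussion point the other way.

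**Conclusion.** The ambiguity is real and should be corrected. As worded, the NRS score may mix pain with an undefined difficulty, and a result for pain intensity could then not be clearly attributed to pain.

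A reader might go further and conclude that the score does mix the two, or that the comparison is diluted or shifted in a known direction. The document does not support that. Mixing depends on which reading applies, and direction and size depend on how difficulty differs between the arms, for which no figure is given. No magnitude is therefore claimed.

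The effect is confined to one secondary outcome. The primary WHO outcome, its 0.5 margin and the sample size of 54 do not depend on the NRS. The verdict assumes that the patient form carries the wording in the article.

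**What to change.** - Anchor the NRS to oral pain only, from no pain to the worst pain imaginable, answered as a whole number from 0 to 10.
- If difficulty is wanted, define it (swallowing, eating, mouth opening or other), ask it as a separate item, list it as an outcome and analyse it separately.
- State what the evaluated parameters are, or remove the phrase if pain is the only one.
- If the form already asks about pain alone, correct the description in the protocol and leave the form as it is.

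The cost is the rewording of one item and its description. Treatment, visits, sample size and the primary analysis do not change. The one downside is that the trial is under way, so any scores already collected with the mixed wording must be flagged.

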### Statistical analysis

Analyses will be performed using Jamovi software (version 2.6.44). Normality will be assessed using the Shapiro-Wilk test, and variables will be described using frequencies and percentages (categorical variables) or means, standard deviations, and medians with interquartile ranges (continuous variables). Baseline comparability between groups will be assessed using Student’s t-test or the Mann-Whitney U test (continuous variables) and the chi-square test or Fisher’s exact test (categorical variables).

The primary outcome, oral mucositis severity (WHO scale), will be analyzed longitudinally using a mixed-effects ordinal logistic regression model to account for the repeated measurements. The model will include treatment group, assessment time, and the treatment vs. time interaction as fixed effects, with participant included as a random effect to account for within-subject correlation. Total radiotherapy dose, tumor location, and concomitant chemotherapy will be included as covariates.

Pain intensity (NRS) will be analyzed longitudinally using an appropriate mixed-effects regression model according to its distribution. The primary analysis will follow the intention-to-treat principle. Missing outcome data will not be imputed; instead, the mixed-effects ordinal logistic regression model will incorporate all available repeated measurements and account for incomplete observations over time under the assumption that data are missing at random.

The primary objective is to determine whether transcutaneous infrared PBMT is non-inferior to intraoral red PBMT regarding oral mucositis severity. Non-inferiority will be assessed using the estimated treatment effect obtained from the longitudinal mixed-effects model and interpreted according to the prespecified non-inferiority margin of 0.5 WHO grade.

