Factors such as patient comfort, logistics, and treatment time also distinguish these modalities. Intraoral PBMT, although it focuses energy directly on the most affected sites (tongue margins, buccal mucosa, soft palate), is more dependent on radiation-induced trismus, which may cause discomfort in patients with severe pain and requires longer session times and closer professional-patient proximity [17, 41, 42, 43]. In contrast, transcutaneous protocols tend to be faster, technically simpler, well-tolerated, and require less application time, which translates to greater feasibility for high-volume services and potential for home use [17, 37, 42, 43]. In hematopoietic transplantation, for example, the duration of the transcutaneous session was approximately one-quarter of the intraoral session, while maintaining similar efficacy in preventing OM [43].

Given this scenario, hybrid or staged strategies are being developed, combining intraoral and transcutaneous PBMT or selecting the approach based on anatomical risk and clinical conditions. Studies using combined protocols in head and neck cancer and in patients undergoing chemotherapy alone show that the combination of intraoral and transcutaneous approaches can further reduce OM scores, improve salivary flow and quality of life, without increasing adverse events [34, 45]. Recent guidelines and reviews suggest that the choice between intraoral PBMT and transcutaneous PBMT should consider not only efficacy but also patient adherence, the pattern of radiation therapy fields, and the need to cover deep or hard-to-reach areas, such as the oropharynx and base of the tongue [16, 17].

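### On-treatment pain is scored only after a laser session that differs by arm, so the secondary NRS comparison mixes mucositis pain with an acute session effect

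*Protocol article*

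**What the plan says.** All references are to the protocol article.

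- **Timing** (Data collection, Pain): "Assessments will be conducted at baseline, immediately following each PBMT session, and during all subsequent follow-up visits". The text names no reading before a session.
- **Recall window** (same place): "Participants will be instructed to mark the point on the scale that most accurately represents their current status for each evaluated parameter". The score is momentary, not a summary since the last visit.
- **Construct** (same place): patients rate "the intensity of the pain or difficulty they are experiencing", which is not restricted to pain from mucositis.
- **Aim** (same place): "This longitudinal monitoring aims to evaluate the patient’s symptomatic response to the intervention over time".
- **Use**: pain intensity is listed under Secondary outcomes as a comparison of the two routes. Under Statistical analysis, "Pain intensity (NRS) will be analyzed longitudinally using an appropriate mixed-effects regression model according to its distribution".
- **Sessions** (Intraoral PBMT, Transcutaneous PBMT, Table 1): 44 points in contact inside the mouth, 440 s in all, against 8 applications on the skin, 80 s in all.
- **Acute effects that the article itself raises**: the Discussion describes the intraoral route as one "which may cause discomfort in patients with severe pain and requires longer session times". The Introduction credits PBMT with analgesic effects.
- **Expected pain result** (Expected results): "transcutaneous PBMT is expected to demonstrate efficacy equivalent to or superior to that of intraoral PBMT", which the article attributes to deeper tissue penetration and modulation of inflammation.

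**The concern.** A between-arm pain comparison in a prevention trial is normally read as telling whether the routes keep mucositis pain equally low. Here each on-treatment score follows directly on the procedure being compared. Short-lived discomfort from more than seven minutes of intraoral contact would raise the IO score and look like a benefit of TC. Immediate relief from light applied directly to the mucosa would lower the IO score and look like a disadvantage of TC.

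At stake is the interpretation of one secondary outcome. If TC scores lower, the reader cannot tell whether it prevented pain better or simply spared patients the intraoral session. The article's explanation through penetration and inflammation could not be checked against these data.

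**Working it through.** **1. Session times.** From the two technique sections and Table 1, time = applications × seconds per application.
- IO: 44 × 10 s = 440 s. This matches the article.
- TC: 8 × 10 s = 80 s. This matches the article.
- Ratio: 440 / 80 = 5.5.

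**2. How much of the pain data is post-session.** Clinical and treatment-related variables gives 30 to 35 fractions at five per week and PBMT three times per week.
- Weeks of RT: 30/5 = 6 to 35/5 = 7.
- Sessions, and so post-session scores per patient: 6 × 3 = 18 to 7 × 3 = 21.
- The number of follow-up visits is not stated. Assuming 0 to 6, the post-session share of all post-baseline scores runs from 18/(18 + 6) = 75% to 100%.

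**3. What the arm difference contains.** Write a post-session score as M + s, where M is the pain present apart from the session and s is the acute effect of that session. Then

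TC − IO = (M_TC − M_IO) + (s_TC − s_IO).

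The first bracket is the question about prevention. The second is the acute effect of the procedure. Randomisation does not cancel it, because the procedure is the arm. The mixed model does not remove it, because an effect that recurs at session visits enters the treatment and treatment-by-time terms. Only a score taken away from the session identifies the first bracket at those visits.

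**4. Scale, on assumptions only.** The documents give no NRS standard deviation and no size for s. Assume 27 patients per arm, one score per patient, M equal in both arms, a shift b = s_TC − s_IO (the sign does not matter) and a two-sided 5% test. Then SE = SD × √(2/27), and the probability of a nominally significant difference is 1 − Φ(1.96 − b/SE) + Φ(−1.96 − b/SE).

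| Assumed SD | SE | b = 0.5 | b = 1.0 | b = 1.5 |
|---|---|---|---|---|
| 2.0 | 0.544 | 15% | 45% | 79% |
| 2.5 | 0.680 | 11% | 31% | 60% |
| 3.0 | 0.816 | 9% | 23% | 45% |

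Example: for SD 2.5 and b = 1.0, SE = 2.5 × √(2/27) = 0.680 and b/SE = 1.47, which gives 31%. Without any session effect the figure would be 5%. The table shows how sensitive the comparison would be if such a shift existed. It does not estimate the shift.

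**The case against.** The best defence is that the timing is deliberate. The article says the score tracks response to the intervention, Study Design and Setting says the aim is to compare the overall clinical performance of each protocol, and the design is called pragmatic. On that view, how a patient feels after a session is part of the effect. This explains why a post-session score is worth having, but it does not make one sufficient. An acute response is a change and needs a pre-session value. A preventive effect needs a score away from the session. Expected results also interprets the pain outcome biologically, not as tolerability.

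Other parts of the defence do stand, and they limit the point:

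- A reader might infer that the NRS measures the procedure instead of mucositis pain. It does not. A post-session score still contains mucositis pain, and the baseline and follow-up scores are not described as post-session.
- A reader might infer a fixed bias at every visit. The only discomfort statement concerns patients with severe pain, and it comes from a general discussion of the literature. The effect is more likely small early in RT and variable later.
- A reader might infer that the bias must favour TC. The analgesic effects credited to PBMT could push the other way.
- The 440 s against 80 s contrast narrows when pain is likely to matter most. Under Standard supportive care protocol, therapeutic 660 nm PBMT for ulcers is not restricted by arm, so TC patients with ulcers would also be treated at the lesion. The contrast does not vanish, because therapeutic irradiation replaces the preventive dose only at coinciding points and the remaining IO points continue.
- A reader might infer bias from the baseline score not being post-session. Baseline precedes treatment in both randomised arms, so its timing alone does not bias the contrast.
- Transient discomfort is to be documented as an adverse effect. That gives some information, but it is not a pain score on the same scale and cannot be subtracted.

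**Conclusion.** The point holds as a confounded secondary comparison. In this open-label trial, a momentary score of pain or difficulty is taken straight after a session that differs by arm, and the text names no pre-session score. The arm difference therefore mixes mucositis pain with an acute session effect, in an unknown proportion and direction.

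Its size cannot be derived from the documents. The 9% to 79% range in the table rests on assumed SDs of 2 to 3, assumed shifts of 0.5 to 1.5 points and a single score per patient. A shift present at only some visits, or narrowed by therapeutic PBMT, would matter less.

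A reader might infer that the main non-inferiority conclusion is compromised. The documents do not support that: the 0.5-grade margin, the sample size and the primary model all concern the WHO grade, which is not shown to depend on when pain is scored. The timeline figure is not available here. If it or the visit form already contains a pre-session NRS, all that remains is to say which score is analysed. This is an inexpensive improvement to one secondary outcome.

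**What to change.** In Data collection (Pain), add an NRS reading before each PBMT session. In Secondary outcomes and Statistical analysis, name the pre-session score as the one used for the between-arm pain comparison. Keep the post-session NRS as a separate measure of tolerability, or use post minus pre as the acute response.

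The cost is one more field on the visit form and a sentence or two in the protocol, with no extra visit. The drawback concerns data already collected: post-session scores are not interchangeable with pre-session scores, so they must be flagged and not pooled with them. Patients enrolled before the change would contribute less to the pain analysis.
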